## Abstract

**Background:**

Up to 60% of patients with bipolar disorder (BD) have a history of traumatic events, which is associated with greater episode severity, higher risk of comorbidity and higher relapse rates. Trauma-focused treatment strategies for BD are thus necessary but studies are currently scarce. The aim of this study is to examine whether Eye Movement Desensitization and Reprocessing (EMDR) therapy focusing on adherence, insight, de-idealisation of manic symptoms, prodromal symptoms and mood stabilization can reduce episode severity and relapse rates and increase cognitive performance and functioning in patients with BD.

**Methods/design:**

This is a single-blind, randomized controlled, multicentre trial in which 82 patients with BD and a history of traumatic events will be recruited and randomly allocated to one of two treatment arms: EMDR therapy or supportive therapy. Patients in both groups will receive 20 psychotherapeutic sessions, 60 min each, during 6 months. The primary outcome is a reduction of affective episodes after 12 and 24 months in favour of the EMDR group. As secondary outcome we postulate a greater reduction in affective symptoms in the EMDR group (as measured by the Bipolar Depression Rating Scale, the Young Mania Rating Scale and the Clinical Global Impression Scale modified for BD), and a better performance in cognitive state, social cognition and functioning (as measured by the Screen for Cognitive Impairment in Psychiatry, The Mayer-Salovey-Caruso Emotional Intelligence Test and the Functioning Assessment Short Test, respectively). Traumatic events will be evaluated by The Holmes-Rahe Life Stress Inventory, the Clinician-administered PTSD Scale and the Impact of Event Scale.

**Discussion:**

The results of this study will provide evidence whether a specific EMDR protocol for patients with BD is effective in reducing affective episodes, affective symptoms and functional, cognitive and trauma symptoms.

**Trial registration:**

The trial is registered at ClinicalTrials.gov, identifier: NCT02634372. Registered on 3 December 2015.

**Electronic supplementary material:**

The online version of this article (doi:10.1186/s13063-017-1910-y) contains supplementary material, which is available to authorized users.

## Background

Bipolar disorder (BD) is a serious neuropsychiatric condition of major public health importance with a complex multifactorial etiology, involving both genetic and environmental factors and associated with high mortality by suicide. BD is characterized by chronic instability of mood, circadian rhythm disturbances and continual fluctuations in energy levels, affect, sleep and cognitive appraisal of the self and others [1]. Although the disorder is conventionally characterized as being episodic in nature, with full recovery between periods of mania and depression, recent data suggest that many bipolar patients do not obtain a complete remission but continue to experience subsyndromal manic or depressive symptoms [2]. This is a clinically important issue since (1) subsyndromal symptoms are associated with a higher risk of relapses and poorer social functioning [3] and (2) interepisode affective instability seems to be refractory to pharmacological treatment [4]. Further possible risk factors for relapses include substance abuse, comorbid anxiety disorders, personality disorders or physical diseases [5].

The intervention strategies available for BD include essentially pharmacotherapy but also, increasingly, psychosocial interventions such as cognitive behavioral therapy, psychoeducation, interpersonal and social rhythm therapy, and family intervention [6]. However, despite the everyday use in clinical practice of both types of intervention, almost 70% of BD patients suffer from at least one affective relapse within 2 to 4 years [7–9].

The comorbidity of posttraumatic stress disorder (PTSD) with BD, with a prevalence of 16 to 39% of bipolar patients [10], might hereby have an important clinical implication. Traumatized bipolar patients suffer from more rapid cycling, more suicide attempts, more substance abuse, have a lower quality of life and more (hypo)manic and depressive symptoms than bipolar patients without PTSD [11, 12]. It is also of concern that early childhood adverse events, not necessarily fulfilling PTDS criteria, can trigger severe mental disorders – such as BD – later in life, with a negative impact on the course of the illness (e.g., [13]). Also, it is well established that adverse life events that occur later in life can negatively affect the course of the disease and can be important contributors to a poorer outcome (e.g., [14]). Studies hereby provide evidence that patients with severe mental illness and traumatic life events show more psychiatric symptoms, increased risk of suicide, increased frequency of risky sexual behaviors, more admissions to psychiatric hospitals and, overall, a greater risk of being re-traumatized [15, 16]. A recent naturalistic study over 4 years found an increase of depressive episodes in BD when patients were experiencing life events 6 months prior to the affective index episode [17].

However, this diagnostic comorbidity with significant negative effects on the prognosis of BD has been until recently largely ignored with an intriguing lack of trials for traumatized bipolar patients.

One form of treatment that is being increasingly used in PTSD is Eye Movement Desensitization and Reprocessing (EMDR) [18]. This integrative psychotherapeutic approach uses standardized protocols and elements of cognitive behavioral, interpersonal, and body-centered therapies in conjunction with dual stimulation (e.g., horizontal eye movements from side to side) [18, 19]. The results of two independent meta-analyses and reviews have shown that EMDR therapy is as effective in the treatment of PTSD symptoms as cognitive behavioral therapy [20–22]. The treatment with EMDR has also recently shown a beneficial and comparable effect to exposure therapy on patients with psychosis and comorbid PTSD in a large randomized controlled trial (RCT) [23]. Our group carried out the first pilot RCT of EMDR in bipolar patients with a history of traumatic events and subsyndromal symptomatology. Results showed that the EMDR intervention not only reduced the symptoms associated with trauma in the patients, but also had beneficial effects on subsyndromal affective symptoms [24]. Following these promising results, our research group has developed a specific and comprehensive EMDR protocol for bipolar patients with a history of trauma [25]. This protocol consists of a detailed survey of traumatic events, the intervention and processing of these events according to the Shapiro standard protocol [19] and five subprotocols directed to (1) mood stabilization, (2) enhancement of treatment adherence, (3) increase insight, (4) treatment of prodromal symptoms and (5) de-idealization of manic symptoms.

We hypothesized that our EMDR Bipolar protocol, as an adjunct to pharmacological treatment would have beneficial effects on the course of the illness of bipolar patients with a history of traumatic events.

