### Participants

The patient sample will consist of 82 patients fulfilling *Diagnostic and Statistical Manual of Mental Disorders, fourth edition, text revision* (DSM-IV-TR) criteria for bipolar I and II disorder, based on clinical interview and review of case notes. Inclusion criteria will be: (1) age between 18 and 65 years, (2) presence of between two and six affective episodes in the last year, (3) current clinical status of euthymia upon clinical evaluation, defined as the presence of clinical remission (Bipolar Depression Rating Scale (BDRS) <8 and Young Mania Rating Scale (YMRS) <6; or subsyndromal status defined as BDRS ≥8 and <14 and/or YMRS ≥7 and <12), (4) presence of one or more traumatic events causing current trauma-related symptoms (The Holmes-Rahe Life Stress Inventory, H-RLSI >0; The Clinician-administered PTSD Scale (CAPS): frequency event >1, intensity of symptom >2; Impact of Event Scale-Revised, IES-R >0), and – following the standard EMDR protocol [19] – Subjective Units of Distress (SUD) >5 (range from 0 to 10, with a score of 10 meaning maximum stress).

Exclusion criteria will be: (1) substance abuse/dependency within 3 months prior to participation (except of nicotine abuse/dependency), (2) neurological disease or brain trauma history, (3) suicidal ideation, (4) previous involvement in trauma-focused therapy, (5) current psychotherapy during the study and months of follow-up.

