### Randomization procedure

All patients meeting the inclusion criteria receive the pretreatment (T0) assessment. After T0, participants will be assigned to EMDR or the ST group by two independent researchers using the following covariate-adaptive allocation procedure [26]: (1) the first two patients will be randomly allocated to EMDR or ST with *p* = 0.5, (2) the next patients will be allocated as follows: (b1) if one group already includes two more patients than the other group, the patient will be randomly allocate to EMDR or ST with *p* = 0.8 for the smallest group and *p* = 0.2 for the largest group, (b2) otherwise, we will first simulate that the patient is allocated to EMDR and calculate the sum of the between-group square standardized differences in age, sex, illness duration and number of affective episodes the year before the clinical trial between groups, we will then simulate that the patient is allocated to ST and recalculate the sum, and finally randomly allocate the patient to EMDR or ST with *p* = 0.8 for the group with the smallest sum and *p* = 0.2 for the group with the largest sum. For example, if we had already included 10 patients to the EMDR group and 8 patients to the ST group, the 19th patient would be randomly allocated with *p* = 0.2 for EMDR and *p* = 0.8 for ST. If they were allocated to ST, we would calculate the above sum of covariates after simulating that the 20th patient is allocated to EMDR and after simulating that is allocated to ST, and if the sum of the EMDR simulation was larger than the sum of the ST simulation, we would randomly allocate the 20th patient with *p* = 0.2 for EMDR and *p* = 0.8 for ST. Following this procedure, final groups should be balanced in size and matched in age, sex, duration and episodes. All steps of the randomization process will be automatically carried out in a central location using a computer program.

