The Clinician-Administered PTSD Scale (CAPS) [34], Spanish validation [35]: the CAPS is the standard scale in the evaluation of the presence or absence of PTSD diagnosis and the frequency and intensity of the symptoms. This scale provides ratings of the frequency and intensity of each of the 17 DSM-IV-TR-based PTSD symptoms on a 0 to 4 Likert-type scale, thereby allowing for a maximal score of 8 for each symptom and a total score range from 0 to 136 [23]. It can be used to diagnose a current or past trauma, or to evaluate symptoms during the last weekThe Impact of Event Scale Revised (IES-R) [36], Spanish validation [37]: the IES-R is a 22-item self-report measure that assesses subjective distress caused by traumatic events. Items correspond directly to 14 of the 17 DSM-IV symptoms of PTSD. Patients are asked to identify a specific stressful life event and then indicate how much they were distressed or bothered during the past 7 days. Items are rated on a 5-point scale ranging from 0 = not at all, 1 = a little bit, 2 = moderately, 3 = quite a bit and 4 = extremely. The IES-R yields a total score (ranging from 0 to 88) and subscale scores can also be calculated for the Intrusion, Avoidance and Hyperarousal subscalesThe Holmes-Rahe Life Stress Inventory [38], Spanish validation [39]. This scale assesses frequency of 43 common stressful life events that occurred over the previous 12 months, providing a standardized measure of the impact of these stressors [40]. Interpretation of the overall score is difficult because of the large differences in each person’s ability to cope and their particular reactions to stress, but there are some general guidelines. Scores below 150 reflect low levels of stress, scores between 150 and 299 represent a 50% risk of illness in the near future and scores above 300 represent an 80% risk of developing a stress-related illness [38]

Cognitive profiles and overall functioning will be evaluated using (see Table 3):

**Table 3 Tab3:** Measurements to evaluate cognitive and functional profiles and satisfaction with the treatment

Clinical variable	Measurement interview/Self-report	T0	T1	T2	T3	T4	T5
		Baseline	Mid-treatment		Post treatment	FU 12 months	FU 24 months
Cognition	SCIP	x			x	x	x
	MSCEIT	x			x	x	x
Functionality	FAST	x			x	x	x
Satisfaction	CLQ-8				x		

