## Statistical analysis

The baseline distribution of sociodemographic and clinical characteristics in each treatment arm will be reported using descriptive statistics.

The main hypothesis of the change in the time to relapse (in weeks) will be analyzed using Cox regressions, and the hypotheses of the changes in the scores of clinical scales as compared to baseline will be tested using repeated measures analyses of variance (ANOVAs) that will include time, treatment arm and their interaction. Those variables that show statistically significant between-arm differences at baseline will be added as covariates in the Cox regressions and repeated measures ANOVAs. For each of the analyses effect size measures (hazard ratio or Hedges’ *g*) will be estimated.

An intention-to-treat (ITT) analysis will be employed to provide unbiased comparisons among the treatment groups, using multiple imputations to deal with the losses of follow-up.

R software will be used to carry out the statistical analyses.

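### Covariates enter the models only after a significant baseline test, so baseline trauma severity (CAPS at T0) would rarely be adjusted for: some precision is lost, without bias

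*Protocol article*

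**What the plan says.** - **Prognosis.** The Background section says that traumatized bipolar patients have "more (hypo)manic and depressive symptoms than bipolar patients without PTSD", and refers to "this diagnostic comorbidity with significant negative effects on the prognosis of BD". It puts PTSD comorbidity at "with a prevalence of 16 to 39% of bipolar patients".
- **Entry.** Participants, inclusion criterion 4, asks for "presence of one or more traumatic events causing current trauma-related symptoms", with thresholds on H-RLSI, CAPS (frequency above 1, intensity above 2), IES-R and SUD (above 5 of 10). A PTSD diagnosis is not required.
- **Measurement.** Under Assessments, "the CAPS is the standard scale in the evaluation of the presence or absence of PTSD diagnosis", with a total score from 0 to 136. Table 2 schedules it at T0, and the Randomization procedure places allocation after T0.
- **Allocation.** The balancing criterion is the "sum of the between-group square standardized differences in age, sex, illness duration and number of affective episodes the year before the clinical trial". CAPS and PTSD status are not in it.
- **Analysis.** "Those variables that show statistically significant between-arm differences at baseline will be added as covariates", in both the Cox regressions and the repeated measures ANOVAs. The Limitations section names one further variable to be taken into account, pharmacological treatment.

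**The concern.** The covariate rule selects on the wrong criterion. A baseline significance test in a randomized trial asks whether an imbalance exceeds chance, which randomization has already answered. Whether adjustment helps depends on how strongly the variable predicts outcome. A prognostic variable should therefore be adjusted for even when the arms look balanced, and a non-prognostic one need not be adjusted for even when they do not.

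Baseline trauma severity is the clearest case here. The article calls PTSD comorbidity prognostic, the tested therapy is aimed at trauma, the score is collected before allocation, and no other step secures balance on it. At stake are the precision of the relapse hazard ratio in a trial of 82 patients and a primary model whose content depends on the observed baseline data. Because the article states the rule, this is not a detail left to an analysis plan that is not shown.

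**Working it through.** **1. The plan's own figure.** The Computation of sample size section gives 36 per group (72 in total) for a hazard ratio of 2, 80% power and alpha 0.005. Two-sided event counts are:

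- Schoenfeld: 4(z₁₋α/₂ + z₁₋β)²/(ln HR)² = 4(2.807 + 0.842)²/0.693² ≈ 111 events.
- Freedman: (2.807 + 0.842)² × ((2 + 1)/(2 − 1))² ≈ 120 events.

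One-sided, the counts are 98 and 106. All exceed 72 patients, so the figure does not reproduce. At two-sided alpha 0.05, Freedman gives (1.960 + 0.842)² × 9 ≈ 71 events, which is 36 per arm only if every patient relapses. This is a separate problem, noted because it limits what covariate adjustment can achieve.

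**2. Size of chance imbalance.** With n per arm and PTSD prevalence p, simple 1:1 allocation gives SD of the difference in PTSD share = √(2p(1 − p)/n). With n = 41:

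- p = 0.30: √(0.42/41) = 0.101
- p = 0.50: √(0.50/41) = 0.110

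The arms then differ by 15 points or more in about 12 to 15% of trials. The prevalence in the enrolled sample is an assumption. At the article's general range of 16 to 39%, a gap of 10 points or more occurs in 17 to 31% of trials of 82, and a gap of 20 points or more in 1 to 5%.

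**3. How often the rule acts.** A 5% test triggers in about 5% of randomized trials, and the simulations in step 5 gave 4.6 to 5.6%. At p = 0.50, significance needs a gap of about 1.96 × 0.110 = 0.216, or roughly 9 of 41 patients. Among trials with a gap of 15 points or more, the rule adjusts only about 40% with a chi-square test and 22 to 25% with Fisher's test.

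**4. Effect of an imbalance on the estimate.** As an approximation, the treatment hazard ratio shifts by the factor (PTSD HR)^gap:

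| Gap in PTSD share | PTSD HR 1.5 | PTSD HR 2 |
|---|---|---|
| 10 points | 1.04 | 1.07 |
| 20 points | 1.08 | 1.15 |

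The shift is equally likely in either direction.

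**5. Power.** Cox models were simulated with 36 per arm, a treatment hazard ratio of 2 between the arms, 70% of controls relapsed at 24 months, PTSD prevalence 16 to 60% and 5,000 trials per scenario. PTSD was a yes/no factor independent of the four balanced variables, and allocation was simple 1:1. The 70% is an assumption based on the Background figure of almost 70% over 2 to 4 years. The gain is for always including PTSD, compared with the plan's rule:

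| PTSD HR for relapse | Gain, two-sided 0.05 (points) | Gain, two-sided 0.005 (points) |
|---|---|---|
| 1.25 | 0.3–0.7 | 0.3–0.9 |
| 1.5 | 0.8–1.2 | 0.6–1.7 |
| 2 | 2.3–3.7 | 1.4–3.7 |
| 3 | 4.8–8.6 | 4.9–7.5 |

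With 41 per arm and control relapse assumed as high as 90%, the gains at two-sided 0.05 are about 1 to 2 points at a PTSD hazard ratio of 1.5 and 2 to 5 points at 2.

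**6. Type I error.** With no treatment effect and PTSD omitted, 3,000 trials per scenario gave rejection rates of 4.9 to 5.4% at nominal 5%.

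**The case against.** The strongest case against is that PTSD may divide this sample only weakly. The Background contrast is between traumatized bipolar patients in general and those without PTSD, whereas every enrolled patient has current trauma symptoms. The entry thresholds, including CAPS intensity above 2 and SUD above 5, narrow the spread further. The Background also says that adverse events short of PTSD worsen the course. Prior-year episode count, which is close to rapid cycling, is balanced and restricted to two to six, mood symptoms are capped at entry, and recent substance abuse is excluded. The residual effect of PTSD on relapse is therefore unknown and could be small. This stands, and it is why the size is given as a range down to about 1 point. It does not defend the rule: a prognostic covariate measured before allocation costs almost nothing to fix in advance.

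It can also be said that CAPS is only one candidate, since the Background names other relapse risk factors such as subsyndromal symptoms. That is fair, and it is why the point rests on the selection rule, with CAPS as the leading example.

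A reader might infer more: that leaving PTSD out biases the relapse comparison, or that imbalanced trials show a distorted result. The documents do not support this. Imbalance is random in direction, the standard error already allows for it, and type I error stays nominal. Nor is PTSD shut out of the analysis, because it can enter through the significance rule.

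**Conclusion.** The concern holds in limited form. Selecting covariates by baseline significance is a poor rule. Under it, a baseline measure that the article treats as prognostic and that the therapy targets is adjusted for in only about 5% of trials, with no balancing to compensate. The consequence is lost precision and uncorrected chance imbalance, not bias.

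The loss is about 1 to 2 power points at two-sided 0.05 for a PTSD hazard ratio of 1.5 and about 2 to 5 points for 2. It is larger only if PTSD is strongly prognostic. These figures rest on assumed prevalence, on 70 to 90% control relapse, and on PTSD being independent of the balanced factors, which if anything overstates the gain. The article supplies no PTSD hazard ratio.

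A reader might also infer that adjustment would restore the planned power. It would not. With 36 per arm and 70% control relapse, power with PTSD always included is still only about 58 to 61% at two-sided 0.05 and 24 to 27% at 0.005. The change is worth making because it is cheap, but it is not the trial's main statistical weakness.

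**What to change.** In the Statistical analysis section, replace the baseline-significance rule with a covariate set named in advance and used whatever the baseline comparison shows. Include the T0 CAPS total score in the Cox regression and in the models for scales other than CAPS. Where CAPS is the outcome, its baseline is already in the repeated measures ANOVA and need not be added.

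Keep the set short. Under the assumptions of the power table the Cox model would have only about 42 events.

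The cost is a sentence or two of text and one degree of freedom for CAPS. No new data are needed. Adding CAPS as a fifth term in the balancing sum is optional and useful only while allocation is open. The sample-size calculation has to be corrected separately.

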## Methods/design

This multicenter collaborative project will involve the participation of three different centers from the Barcelona catchment area, Spain (Hospital Benito Menni, Hospital Clinic of Barcelona and Hospital del Mar). EMDR and supportive therapy (ST) therapists have extensive experience in the application of both psychotherapies. EMDR therapists have already participated in the pilot study [24] and all therapists received a detailed day training in applying the EMDR therapy protocol and a well-defined ST program. The application of all clinical assessments has been defined and practiced within all participating raters. All centers and research groups involved have wide ambulatory facilities and outpatient clinics for BD patients that will facilitate meeting the recruitment criteria and development of this project.

### Study aim

The overall aim of this study is to examine whether the EMDR Bipolar protocol for BP with a history of traumatic events can reduce affective relapses, improve affective and trauma-related symptoms and result in a better performance in cognition and psychosocial functioning, when compared ST. Other related aims of this trial are to expand the available options for psychosocial intervention in BD, to explore that the EMDR therapy is a safe and effective tool in traumatized bipolar patients and that treatment with EMDR leads to an improvement in the course and prognosis of the disease.

Based on our pilot study of EMDR in traumatized bipolar patients, we propose the following hypotheses:The EMDR group will show fewer affective relapses at 12 and 24 months’ follow-up compared to the ST groupPatients in the EMDR group will show fewer affective and trauma-related symptoms compared to the ST group at evaluations after 6 months of therapy, at 12 and 24 monthsPatients in the EMDR group will show a better cognitive and psychosocial functioning compared to the ST group at evaluations after 6 months of therapy, at 12 and 24 months

